#### Intervention

The primary, intention-to-treat (ITT) analyses will evaluate the impact of the intervention, both in terms of a) return to below-threshold levels for CMD and CVD/DM risk (i.e. dichotomized outcomes), and b) improvement in the levels of the continuous CMD and CVD/DM measures (depression and anxiety scores, BP, HbA1c, LDL, and serum creatinine levels) via logistic and linear mixed-effects regression models respectively, with repeated measures nested within individuals, and individuals nested within PHC, and random intercepts for individuals and PHC [96, 97]. The trajectories of the continuous variables will be examined via the time-by-intervention interaction effect. We will run separate regressions for the various outcomes, to allow us to detect if different variables react to the intervention at different rates. To prevent Type I error inflation, we will lower α accordingly. In all models covariates will be included as necessary.

The sample size of 1250 in each intervention arm (50 participants per PHC), was determined based on achieving 80% power for the ITT analyses regarding the effect of the intervention, and was calculated as follows: we assumed an attrition rate of 20%, and an intra-class correlation (ICC) of 0.1 to account for clustering of participants in PHCs, which reduces the initial sample size to an effective sample size of *n* = 204/group. Pooling data across the three post-intervention measurements triples this number, and subsequent adjustment for repeated measures with an assumed ICC = 0.5, results in a final *effective* sample size of *n* = 306 person-time observations per group. Based on previous research, we assumed 40% of control group participants to recover [98, 99]. With α = .025, the minimum detectable effect size at 80% power is 12% more of the intervention group participants recovering [100]. This is a small effect size according to Cohen [101], and comparable to earlier studies in the US [26]. To test the screening hypothesis, with 25 PHCs per screening condition, 80% power and α = 0.05, the minimum detectable effect in a Poisson regression is 2.1 times as many co-morbid cases identified with the enhanced compared to the standard screening [102]. Although this is a large effect, we deemed it attainable, given the documented under-reporting of mental health in standard care [10, 11], and the intensive nature of our enhanced screening.

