**Methods:**

This study is a multi-level randomized controlled trial among patients with depression or anxiety and co-morbid diabetes, or cardiovascular disease. Aim 1 examines whether patients screened at community health-fairs are more likely to be diagnosed and treated for these co-morbid conditions than patients screened after presenting at PHCs. Aim 2 evaluates the impact of collaborative care compared to usual care in a cluster RCT, randomizing at the level of the PHCs. Intervention arm PHC staff are trained in mental health diagnoses, treatment, and the collaborative care model. The intervention also involves community-based “Healthy Living groups” co-led by Ashas, using cognitive-behavioral strategies to promote healthy behaviors. The primary outcome is severity of common mental disorders, with secondary outcomes being diabetes and cardiovascular risk, staff knowledge and patient perceptions.

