#### Community-based intervention

Participants in the intervention PHCs are given an appointment to participate in a 12-month, healthy living group, designed to target risk factors important in management of depression, anxiety, DM, and CVD (Table 2). Each group includes eight to 10 same-sex participants and held in an easily accessible venue in the community. The first 12 weekly sessions are facilitated by a master’s level counselor and co-facilitated by an ASHA, who subsequently provides nine monthly sessions focused on behavior maintenance. The behavioral change strategies used are based on principles of social cognitive theory, such as observational learning, setting manageable goals, practice and getting feedback, building self-efficacy and skills training [69, 70].

**Table 2 Tab2:** Community-based Healthy Living Group Session Topics and Exercises

Session #	Topics covered	Exercises
1	CVD risk factors and diabetes	Discuss modifiable and non-modifiable behavioral risks
2	Psychological well-being, depression, anxiety and stress	Identify sources of and strategies to reduce depression, anxiety, and stress
3	Role of nutrition in disease	Review eating habits and develop plan to eat healthier
4	Improving physical and emotional health with exercise	Strategies for overcoming obstacles and creating a habit to exercise on a regular basis
5	Smoking and smokeless tobacco cessation	Discuss harmful effects of tobacco, triggers, and strategies for quitting
6	Alcohol use	Discuss harmful effects of alcohol, triggers, and strategies for quitting
7	Social support for behavior change	Sources of emotional, practical, and informational, strategies for approaching family, friends, and community for support, identify social support needs. Communication skills to use with unsupportive people.
8	Quality of life	Assessing quality of life and identifying strategies to improve quality of life
9	Tools for initial behavior change	Self-monitoring, goal setting, self-reinforcement, setting up an environment that supports change
10	Review of sessions 1-9	Identify successes and barriers to behavior change
11, 12	Long term maintenance of behaviors. Different strategies needed for initial change	Setting and reaching behavior change goals by using strategies learned in previous sessions
Monthly	Behavioral maintenance session	Review accomplishments, problem solving barriers, revising plans, utilizing group support

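### The time-by-intervention test sits in a model with random intercepts for individuals and PHC, so variation between PHCs in change over time is missing from its standard error

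*Protocol article*

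**What the plan says.** The Abstract (Methods) describes Aim 2 as a "cluster RCT, randomizing at the level of the PHCs" and states that "The primary outcome is severity of common mental disorders". The Intervention part of the Statistical analyses section defines the ITT analyses as logistic models for dichotomised outcomes and linear mixed models for continuous ones, the latter including depression and anxiety scores. Visits are nested in individuals and individuals in PHCs, and the random effects and the test are given together: "random intercepts for individuals and PHC [96, 97]. The trajectories of the continuous variables will be examined via the time-by-intervention interaction effect".

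The section names no random slope, PHC-by-time term, robust variance or other device that would let PHCs differ in their course over time. It does undertake to lower α against Type I error inflation. That sentence follows the one on separate regressions for the various outcomes, so it concerns multiplicity and not this point.

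The sample size paragraph does allow for clustering, with a PHC ICC of 0.1, but it applies this to recovery proportions pooled over the post-intervention visits.

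**The concern.** The article fixes both the random-effects structure and the test, and the two do not fit together. A random intercept for PHC says that some PHCs have higher scores than others by the same amount at every visit. Subtract one visit from another and the term is gone. The time-by-intervention contrast is then judged against patient-level residual error, as if about 1000 individuals per arm had been allocated independently.

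PHCs can be expected to differ in change. Treatment is delivered by each PHC's own physician, nurses and ASHAs, and it acts after baseline, so an intercept that is constant from baseline onward cannot absorb its variation. The depression and anxiety scores, which carry the stated primary outcome, are among those whose trajectories are tested this way. At stake are false claims that the arms diverge over time, and overstated precision for any divergence that is real.

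**Working it through.** **Inputs from the article.** The plan has "The sample size of 1250 in each intervention arm (50 participants per PHC"), hence 25 PHCs per arm. Attrition is 20%, PHC ICC 0.1, repeated-measures ICC 0.5 and α 0.025. Visits are at 0, 1.5, 3, 6 and 12 months.

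**The plan's own figures.** 1250 × 0.8 = 1000 per arm, or 40 per PHC. Design effect 1 + 39 × 0.1 = 4.9, and 1000 / 4.9 = 204. Then 3 × 204.1 / (1 + 2 × 0.5) = 306. With 306 per group, 40% control recovery and α 0.025 two-sided, 80% power needs a difference of 12.4 points, which agrees with the stated 12% after rounding. The planning values therefore reproduce.

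**What the stated model uses for the interaction.** With total variance 1 and within-person variance 0.5, the squared deviations of the visit times from their mean (4.5 months) sum to 20.25 + 9 + 2.25 + 2.25 + 56.25 = 90. The model-based variance of the slope difference is 2 × 0.5 / (1000 × 90) = 0.0000111, so SE = 0.00333 per month. The number of PHCs does not appear. A fit of the three-level random-intercept model to simulated data gave 0.00335.

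**What it should use.** Let CAC be the correlation of a PHC's effect between two visits. **The article does not give CAC, so it is an assumption and is varied.** The PHC-by-time variance is 0.1 × (1 − CAC), and its share of within-person variance is ρ = 0.1 × (1 − CAC) / 0.5. In a balanced design the true variance exceeds the model's by D = 1 + (40 − 1)ρ. For CAC 0.8, ρ = 0.02 / 0.5 = 0.04 and D = 1 + 39 × 0.04 = 2.56. Directly per PHC, the true variance term is 0.02 + 0.48/40 = 0.032, the model's is 0.5/40 = 0.0125, and the ratio is again 2.56.

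Actual two-sided Type I error is 2 × [1 − Φ(z / √D)], with z = 1.960 for nominal 0.05 and 2.241 for nominal 0.025:

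| CAC (assumed) | D | √D (SE ratio) | Error at 0.05 | Error at 0.025 |
|---|---|---|---|---|
| 1.0 | 1.00 | 1.00 | 0.050 | 0.025 |
| 0.98 | 1.16 | 1.08 | 0.068 | 0.037 |
| 0.95 | 1.39 | 1.18 | 0.096 | 0.057 |
| 0.9 | 1.78 | 1.33 | 0.142 | 0.093 |
| 0.8 | 2.56 | 1.60 | 0.221 | 0.161 |

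**Simulation** (25 PHCs per arm, 40 patients each, five visits, 3000 runs per setting, linear time) gave 0.050, 0.088, 0.145 and 0.210 at nominal 0.05 for CAC 1.0, 0.95, 0.9 and 0.8. A 12-month-versus-baseline contrast gave similar results. A test on PHC-level changes stayed at about 0.045 to 0.055. Fitting the stated model itself at CAC 0.8 rejected in 25% of 193 fits, with some convergence warnings.

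**Expressed as a PHC slope instead.** Slope SDs of 0.05, 0.1, 0.15 and 0.2 total SDs over 12 months gave 0.060, 0.108, 0.173 and 0.252.

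**Sensitivity to the PHC ICC.** With ICC 0.05 and CAC 0.9, ρ = 0.005 / 0.5 = 0.01, D = 1.39 and the error is 9.6%. With ICC 0.02 and CAC 0.9, ρ = 0.004, D = 1.16 and the error is 6.8%. With ICC 0.02 and CAC 0.95, it is 5.9%. These lower ICCs are assumptions.

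**The case against.** A reader might infer that the Type I error for the primary outcome is inflated several-fold, or that all of Aim 2 is compromised. The article supports neither.

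- **Size.** Inflation of two-fold or more needs two inputs together: a PHC ICC near 0.1 for these scores and a CAC of about 0.95 or below. The article gives 0.1 as a planning value for recovery, not for change in continuous scores, and it gives no CAC. At CAC 0.98 the factor is only 1.4, and at 1.0 there is no inflation. This objection stands, and the size must be stated conditionally.
- **Scope.** The primary analyses comprise return below threshold and improvement in continuous levels. The interaction is named for trajectories, and nothing says that it is the sole confirmatory test. The powered contrast is recovery pooled over post-intervention visits. A treatment main effect on post-intervention levels or proportions keeps the PHC intercept variance. This also stands, and the point is confined to the interaction test.
- **Healthy Living groups.** These groups of eight to 10 lie below PHC level and exist only in the intervention arm. Clustering by group is a different structure and is not needed for this point.
- **A condensed article.** A full analysis plan may add random slopes, and the choice of degrees-of-freedom method or convergence fallback is properly left to it. But the article does not leave the random effects open. It states intercepts and then names a test for which the PHC intercept offers no protection, so the wording needs correction.

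**Conclusion.** The point holds for the time-by-intervention interaction. As written, its standard error omits between-PHC variation in change although PHCs were the randomised units. The test is valid only if PHCs within an arm share the same underlying course. Otherwise it rejects too often and its intervals are too narrow.

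For CAC between 0.95 and 0.8, actual error at nominal 0.05 is roughly two- to four-fold (about 10% to 22%). This rests on 40 patients per PHC in a balanced design, on the planning ICCs of 0.1 and 0.5 carrying over to the continuous scores, and on the assumed CAC. The direction of the error does not depend on these values, but its size does.

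**What to change.** In every model that tests time-by-intervention, add a PHC-level random slope for time or a PHC-by-visit random effect, or use an equivalent PHC-level analysis of change. Base inference on the 50 PHCs. The wording could read: random intercepts for individuals and PHC, plus a PHC-level random effect for change over time.

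No data collection changes, and the article reports that assessments were still ongoing. The cost is one further variance component, occasional convergence work and wider intervals. For CAC 0.95 to 0.8 the interaction's standard error grows by a factor of about 1.2 to 1.6, which is the precision that the design actually provides under those assumptions.

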#### Blood pressure (BP)

Systolic and diastolic blood pressure is measured using a standardized protocol. Two measurements are taken and the average of the two readings is calculated [86, 87]. Hypertension is defined as elevated blood pressure (average systolic BP (SBP) ≥ 140 mmHg and/or an average diastolic BP (DBP) ≥90 mmHg) or higher levels of hypertension if SBP ≥ 160 mmHg and/or an DBP ≥ 95 mmHg.

*Body Mass* Index (BMI) is calculated as weight (kg) divided by height (m^2^) [78]. Waist circumference is measured in centimeters.

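### The Abstract makes diabetes and cardiovascular risk secondary, but the Intervention analysis lists them unranked among the primary ITT analyses, and the power α of .025 fits two tests, not the eight or so listed

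*Protocol article*

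**What the plan says.** The Abstract (Methods) ranks the outcomes: "The primary outcome is severity of common mental disorders, with secondary outcomes being diabetes and cardiovascular risk, staff knowledge and patient perceptions".

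Statistical analyses, Intervention, describes what it calls the primary intention-to-treat analyses in two parts. Part (a) is dichotomised and covers both CMD and CVD/DM risk. Part (b) is continuous and lists "depression and anxiety scores, BP, HbA1c, LDL, and serum creatinine levels". Nothing in the sentence ranks one domain above the other. Each outcome has its own regression, and the continuous trajectories are examined through the time-by-intervention interaction. On multiplicity the text says "To prevent Type I error inflation, we will lower α accordingly", with no number of tests.

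The sample size paragraph of the same section assumes 40% recovery in the control group and pools three post-intervention measurements into an effective 306 observations per group. It then states: "With α = .025, the minimum detectable effect size at 80% power is 12" per cent more recovering. It does not say why α is .025. The screening hypothesis has its own calculation at α = 0.05, so .025 is not a division of .05 between the screening and intervention questions.

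**The concern.** Three statements about the main comparison do not fit together.

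- **Outcome hierarchy.** Cardiometabolic outcomes are secondary in the Abstract and part of the primary analyses in the Intervention section.
- **Size of the family.** α is to be lowered across separate regressions on at least six continuous and two dichotomised outcomes, yet power is computed at an α that fits two tests.
- **Form of the outcome.** The declared primary outcome is severity. The only power figure is for binary recovery pooled over visits. The contrast given for the continuous trajectories is a time-by-intervention interaction, for which no power is stated.

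At stake is which result makes the trial positive, and whether the 80% power claim applies to that result. An analysis plan written later cannot satisfy both the Abstract and the Intervention section as they stand.

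**Working it through.** **Inputs**, all from Statistical analyses, Intervention: 1250 per arm in 25 PHCs of 50; attrition 20%; cluster ICC 0.1; three pooled measurements with ICC 0.5; control recovery 40%; α = .025; power 80%.

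**1. The plan's effective sample size.**
- After attrition: 1250 × 0.8 = 1000 per arm, or 40 per PHC.
- Cluster design effect: 1 + (40 − 1) × 0.1 = 4.9, and 1000 / 4.9 = 204.
- Repeated measures: 204 × 3 = 612; design effect 1 + 2 × 0.5 = 2; 612 / 2 = 306.

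Both stated figures, 204 and 306, are reproduced.

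**2. The plan's detectable difference.** With p₁ = 0.40, p₂ = p₁ + d, p̄ their mean and n = 306 per group,

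power = Φ{ [d − z₁₋α/₂ √(2p̄(1 − p̄)/n)] / √[(p₁(1 − p₁) + p₂(1 − p₂))/n] }.

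Solving for 80% power gives d = 12.4 points at two-sided .025 and 11.3 points at two-sided .05 (which is one-sided .025). The stated 12 therefore fits two-sided .025, that is .05/2. At exactly 12 points the power is 77.1%; the gap from 80% is rounding, and 77% is the right baseline below.

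**3. The count of tests.** Part (b) names depression, anxiety, BP, HbA1c, LDL and serum creatinine: six, with BP counted once. Part (a) names CMD and CVD/DM risk: two. The minimum is 6 + 2 = 8. It is larger if systolic and diastolic pressure are tested separately, or if each measure has its own threshold. A family limited to CMD, with PHQ-9 and GAD-7 each in continuous and dichotomised form, has four.

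**4. Power if .05 is split equally.** At 40% versus 52%, the null standard error is √(2 × 0.46 × 0.54/306) = 0.0403 and the alternative is √((0.24 + 0.2496)/306) = 0.0400. For eight tests: (0.12 − 2.734 × 0.0403)/0.0400 = 0.246, and Φ(0.246) = 0.597.

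| Family | Tests | α per test | Power, 40% v 52%, n = 306 | Detectable difference at 80% | Effective n per group for 80% at 12 points |
|---|---|---|---|---|---|
| Matching the plan's α | 2 | .025 | 77.1% | 12.4 points | 327 |
| CMD only, both forms | 4 | .0125 | 68.6% | 13.4 points | 384 |
| Minimum count as listed | 8 | .00625 | 59.7% | 14.4 points | 440 |

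**5. Error rate if .025 is used for every test.** Under independence, 1 − 0.975⁸ = 18.3%. Whatever the dependence, the Bonferroni bound is 8 × .025 = 20%. With two tests the independence figure is 4.9%.

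**The case against.** The best defence reads the word primary in the Intervention section as marking the main analysis approach, as against the preliminary and screening analyses described just before it, and not as ranking outcomes. The Abstract would then supply the hierarchy, .025 would be .05 shared between PHQ-9 and GAD-7, and the remark about lowering α might refer to that same division. This is coherent, and it is probably close to what was intended. But the article does not say it. The sentence puts both domains side by side, and the α remark follows directly on separate regressions for all the outcomes. Even a CMD-only family, with both scales in both forms, has four tests.

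It is also fair that the exact multiplicity method may be left to an analysis plan not shown here. Its absence is not the point; the conflict inside the article is.

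Several stronger inferences are tempting and should not be drawn.

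- **That the family has 14 tests.** This would need systolic and diastolic pressure tested separately and a dichotomised version of every measure. The article gives no recovery threshold for serum creatinine, for example.
- **That either the power is wrong or the error rate is uncontrolled.** A gatekept order with CMD first could keep .025 for CMD and control the family-wise error. None is described, but it is not excluded.
- **That success could be claimed on LDL or creatinine.** The article states no success rule, and the Abstract places those domains among the secondary outcomes.
- **That the Abstract demotes CMD recovery.** It does not mention dichotomised CMD, and recovery is the outcome on which the trial was powered.

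**Conclusion.** The point stands as an internal conflict. The Abstract and the Intervention section disagree on whether cardiovascular and diabetes outcomes are primary. The α used for power fits two tests where the text lists at least eight. The power figure is for recovery, while the named primary outcome is severity.

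If .05 were split equally over eight tests, power for 40% versus 52% would be about 60% instead of about 77%, or about 69% for a CMD-only family of four. If .025 were applied to all eight, family-wise error would be about 18% under independence.

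These sizes are conditional. Eight is a count made from the text, not a figure that the article states. The power losses assume an equal Bonferroni split; a gatekept or stepwise procedure would lose less. A score and its dichotomised version are strongly related, so the true family-wise error would probably be below 18%, and it cannot exceed 20%. The effective n of 306 is taken as the plan gives it. The power figures apply to recovery; power for severity cannot be worked out from the article.

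**What to change.** Rewrite the Intervention section to agree with the Abstract:

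- Name two primary tests, one on PHQ-9 and one on GAD-7, on one stated contrast, each at .025 or by Holm at .05 overall.
- State whether CMD severity or CMD recovery is the primary form, and make the other secondary. Either choice is coherent. Choosing recovery would mean changing the Abstract; choosing severity would mean a new power statement.
- Label all cardiovascular and diabetes measures secondary, tested after the primaries.
- Give the power for the named contrast at the named α, and say what .025 was divided for.

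The cost is wording and one power calculation; no design feature changes. The article reports intervention and assessments as ongoing, so the hierarchy should be fixed before outcomes are analysed by arm. The downside is that cardiovascular and diabetes results cannot be called primary, which the Abstract already concedes, and that the stated power may become less favourable.

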#### Collaborative care staff training

Staff in the 25 intervention PHCs receive training sessions in the collaborative care model [26] by psychiatrists from St John’s Medical College, who have volunteered to take on the role of “consultant psychiatrist” [78]. The PHC staff training is designed to enable them to effectively integrate treatment of CMDs into their regular practice in patients with co-morbid medical conditions. A modified version of the IMPACT model [48, 78] was adapted for our setting to maximize the likelihood of sustainability. PHC staffs are required to undergo one full day of interactive group training. The morning session trains all PHC staffs on management of chronic non-communicable diseases at the clinic level and the second half focuses on collaborative care in mental health. Primary care physicians are trained to identify and treat patients presenting with a CMD. The PHC nurses are trained to function as “care managers,” and help with tracking patient progress. Support is also being provided by the consulting psychiatrists, who provide both routine caseload, diagnostic, and treatment consultation for difficult cases, which may include referral recommendations when additional care is needed. Other care team members include the PHC pharmacist, trained to educate patients and their caregivers about their medication regimen, side effects and adherence. Finally, the ASHAs are trained in risk factor screening and modification, and act as a liaison between the PHC, patients, families and community. They co-facilitate the healthy living groups and provide appointment reminders through home visits.

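### The effective sample size of 306 per group exceeds the ceiling of 250 set by the plan's own PHC count, ICC and model; power for a 12-point recovery difference is about 60%, not 80%

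*Protocol article*

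**What the plan says.** The sample-size paragraph is in the Protocol article under Statistical analyses, Intervention. It starts from "The sample size of 1250 in each intervention arm (50 participants per PHC"), applies 20% attrition, and allows for "an intra-class correlation (ICC) of 0.1 to account for clustering of participants in PHCs". After these two steps, 204 per group remain.

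It then adds a gain for repeated visits: "Pooling data across the three post-intervention measurements triples this number, and subsequent adjustment for repeated measures with an assumed ICC = 0.5". The result is 306 person-time observations per group. With 40% recovery assumed in the control group and alpha 0.025, it concludes that "the minimum detectable effect size at 80% power is 12% more of the intervention group participants recovering".

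The paragraph before it sets the analysis model: repeated measures within individuals, individuals within PHCs, and "random intercepts for individuals and PHC".

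**The concern.** The order of the two adjustments matters. The variance of an arm mean has a between-PHC part, a between-person part and a visit-to-visit part. More visits per person shrink only the last. Multiplying the cluster-deflated 204 by 3/2 divides all three parts by 1.5, including the PHC part, which is the largest here and which the stated model holds constant over visits.

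The paragraph says the enrolment figure was chosen to give 80% power for the intention-to-treat analyses, and this is the calculation offered in support. If the effective size is overstated, readers would judge a null result against a sensitivity that the design lacks. At 62% power the chance of missing a true 12-point benefit is about 38%, nearly double the stated 20%.

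**Working it through.** **Inputs** (Protocol article)
- 1250 enrolled per arm, 50 per PHC; attrition 20%; PHC ICC 0.1; three pooled visits; repeated-measures ICC 0.5; control recovery 40%; alpha 0.025; power 80%. All are from Statistical analyses, Intervention.
- 25 PHCs per arm, from Collaborative care staff training ("Staff in the 25 intervention PHCs receive training sessions"); 1250/50 = 25 agrees.
- After attrition: 1000 per arm, 40 per PHC.

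**Reproducing the plan's figures**
- Design effect: 1 + (40 − 1) × 0.1 = 4.9. Effective n: 1000/4.9 = 204.1.
- Repeated measures: 204.1 × 3 / (1 + 2 × 0.5) = 612.2/2 = 306.1.
- Detectable difference at n = 306, 80% power, two-sided alpha 0.025 (normal approximation, unpooled variance): 12.3 points, printed as 12. A one-sided alpha of 0.025 would give 11.2, so the two-sided reading fits better.

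Both printed sample sizes are matched, so the route is clear.

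**Ceiling**

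Take total variance as 1. With a PHC effect that is the same at every visit, the variance of an arm mean cannot fall below 0.1/25. Effective n therefore cannot exceed 25/0.1 = 250, however many patients or visits are added. With 40 patients per PHC and unlimited visits the limit is 25/(0.1 + 0.4/40) = 227. The claimed 306 is above both.

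**Effective n on the plan's inputs**
- If 0.5 is the total within-person correlation, the variance parts are 0.1 (PHC), 0.4 (person) and 0.5 (visit): 25/(0.1 + 0.4/40 + 0.5/120) = 25/0.11417 = 219.0.
- If 0.5 is the correlation within a PHC, the parts are 0.1, 0.45 and 0.45: 25/(0.1 + 0.45/40 + 0.45/120) = 25/0.115 = 217.4.
- The outcome schedule has four post-baseline visits. Using four: 25/(0.1 + 0.4/40 + 0.5/160) = 221.0.

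Pooling three visits raises the effective size from 204 to about 219, not to 306.

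**Power and detectable difference**

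Power for 40% versus 52% is Φ(0.12/SE − 2.241), with SE = √[(0.40 × 0.60 + 0.52 × 0.48)/n] = √(0.4896/n).
- n = 219: SE = 0.0473, 0.12/SE = 2.538, power = Φ(0.297) = 61.7%.
- n = 306: SE = 0.0400, 0.12/SE = 3.000, power = Φ(0.759) = 77.6%.

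| Effective n | Power for 12 points | Same, t on 48 df | Difference detectable at 80% (normal) |
|---|---|---|---|
| 306 (plan) | 77.6% | 75% | 12.3 points |
| 250 (ceiling) | 68% | 66% | 13.6 points |
| 219 | 61.7% | 59% | 14.6 points |
| 217 | 61% | 59% | 14.6 points |

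The 48 degrees of freedom are the 50 PHCs less 2. On that reference the detectable difference at n = 219 is 14.9 points.

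**The case against.** Four points can be made for the plan.

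- **The ceiling is conditional.** It assumes a PHC effect that is constant over visits. The article states this for the analysis model, not expressly for the planning step. If PHC effects correlated only 0.5 between visits, the effective size would be 306. This limits the wording: 306 is unattainable under the stated model, not under every model. The article gives no such assumption, and a PHC random intercept alone excludes it. Correlations of 0.9 and 0.8 would give only 232 and 247.
- **Some of the gap is not the clustering step.** At n = 306, power for exactly 12.0 points is already 77.6%, because 12.3 was rounded to 12. The clustering step accounts for about 16 points (77.6% to 61.7%). The 59% also uses a t reference that the plan did not state. This stands, which is why the parts are shown separately.
- **Sidedness is not stated.** With one-sided alpha 0.025, power at n = 219 would be 72% and the detectable difference 13.2 points. The stated 80% still fails.
- **Scope and validity.** The calculation concerns the dichotomised recovery outcome pooled over visits. The continuous outcomes are examined through the time-by-intervention interaction, where a constant PHC intercept cancels, so the 250 ceiling does not govern that test. The planned mixed model is also multilevel, so the error does not bias estimates or inflate Type I error. Both points stand; they limit the finding to the power claim for recovery.

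**Conclusion.** The concern holds. The figure of 306 follows from the plan's steps, but one of those steps is invalid under the plan's own model. The stated inputs give an effective size of 217 to 219 per group. For the pooled recovery comparison, power for a 12-point difference is about 62% (59% with t on 48 degrees of freedom), and the difference detectable at 80% power is about 14.6 points (14.9 with t).

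This rests on the plan's own ICCs, attrition and control rate, on a PHC effect constant over visits as the model specifies, and on a two-sided reading of alpha, which is an assumption. No reading of sidedness, of the 0.5 ICC or of the number of visits restores 80% power while the PHC effect is constant.

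**What to change.** Replace the two-step deflation in the sample-size paragraph with the three-level calculation: effective n = 25/[0.1 + (0.5 − 0.1)/40 + (1 − 0.5)/(40 × 3)] = 219 per group. State whether 0.5 is the total or the within-PHC correlation, and whether alpha is two-sided. Then report either a detectable difference of about 14.6 points (54.6% versus 40%) at 80% power, or power of about 60% for 12 points, and say that this applies to the pooled recovery outcome. If the sponsor believes PHC effects vary between visits, the assumed between-visit correlation should be stated and the model extended to match.

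The remarks that the effect is small and comparable to earlier studies are tied to the 12-point figure and should be rechecked.

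The cost is rewording and a less favourable stated effect. Enrolment, visits and procedures do not change.
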